Engaging people with PD in treatment is a major challenge [19,20]. The social problem solving approach enhances engagement by offering an accessible framework for change (i.e., the approach appeals to common sense), supporting people in the experience of successful problem solving (i.e., increasing the likelihood of reinforcement of the developing skills), and encouraging independence rather than reliance on therapy (i.e., promoting self-efficacy). Furthermore, PEPS therapy has a preliminary psycho-education component which aims to educate, build rapport, and motivate people for problem solving therapy [21]. Personality disorders and their impact are discussed in a collaborative dialogue and problems that may be worked upon in group sessions are identified.

PEPS therapy has been evaluated with community adults with PD in a Phase 2 exploratory trial [22]. At the end of treatment, compared to a wait-list control group, those treated with PEPS therapy showed better social functioning, as measured by the Social Functioning Questionnaire [23]. All aspects of social problem solving improved over the course of PEPS therapy, and, after controlling for baseline level of social functioning, the most important predictor of improvement in social functioning was a reduction in negative problem orientation, i.e., people felt less threatened by problems and more confident in their ability to solve them [24].

This exploratory study has been identified as important in four ways [25,26]. First, the intervention was brief and hence is likely to be more acceptable to many patients than lengthier interventions; this decreases the likelihood of drop-out and may also be more acceptable to services with limited resources. Second, PEPS therapy was delivered in clinical settings, hence its likely effectiveness in everyday practice was indicated. Third, PEPS therapy was offered to people with any PD or combination of PDs, so it was inclusive rather than exclusive. Fourth, PEPS therapy was delivered by non-specialist staff, hence it would be possible to deliver it relatively cheaply.

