### Study Hypotheses

Our primary hypothesis is that, compared with those in treatment-as-usual, those in PEPS therapy will show a greater improvement in social functioning post-therapy and at follow-up 72 weeks post-randomisation. Secondary hypotheses are that, compared with those in treatment-as-usual, those in PEPS therapy will show the following changes both immediately after therapy and at follow-up: (a) a greater reduction in receipt of unscheduled services; (b) a greater increase in receipt of scheduled services; (c) a greater improvement in quality of life; (d) a greater improvement in referrers' ratings of functioning; (e) a greater reduction in anxiety and depression; and (f) improvement on client-ratings of self-identified three key problems. Regarding intermediate changes, we hypothesise that, compared with those in treatment-as-usual, those in PEPS therapy will show: (a) better therapist alliance after psycho-education; and (b) a greater improvement in social problem solving at end of therapy. We also expect PEPS therapy to show an acceptable level of cost-effectiveness, based on thresholds that appear to guide National Institute for Clinical Excellence (NICE) recommendations.

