### Sample size

The sample size was calculated on the basis of the primary hypothesis. In the exploratory study [22], those referred to PEPS had a greater improvement in social functioning at 6 month follow-up equivalent to 1.05 points on the SFQ. However, a number of people received PEPS who were not included in the trial (e.g., the wait-list control) and, for this larger sample (N = 93), the mean pre-post- treatment difference was 1.79 (pre-treatment mean = 13.85, SD = 4.21; post-treatment mean = 12.06, SD = 4.21). (Note: a lower SFQ score is more desirable). This difference of almost 2 points accords with other evidence that this is a clinically significant and important difference [29]. A reduction of 2 points or more on the SFQ at 1 year follow-up in an RCT of cognitive behaviour therapy in health anxiety was associated with a halving of secondary care appointments (1.24.vs 0.65), a clinically significant reduction in the Hospital Anxiety and Depression Scale (HADS [30]) Anxiety score of 2.5 (9.9 vs 7.45) and a reduction in health anxiety (the main outcome) of 5.6 points (17.8 vs 12.2) (11 is a normal population score and 18 is pathological) [29]. These findings suggest that improvements in social functioning may accrue over 1 year, hence we expect to find a greater magnitude of response at the 72 week follow-up than we did in the exploratory trial. Therefore, we have powered this trial to be able to detect a difference in SFQ score of 2 points. SFQ standard deviations vary between treatment, control, and the wait-list samples, ranging from 3.78 to 4.53. We have based our sample size estimate on the most conservative (i.e., largest) SD. To detect a mean difference in SFQ score of 2 point (SD = 4.53) at 72 weeks with a two-sided significance level of 1% and power of 80% with equal allocation to two arms would require 120 patients in each arm of the trial. To allow for 30% drop out, 170 will be recruited per arm, i.e., 340 in total. We have considered the need to take clustering effects by therapy group into account. In this study, as in the pilot, participants are individually randomised to the treatment arms, and the observed SD of the response in the intervention arm automatically includes the effect of the clustering by therapist. The analysis will take account of this by using a hierarchical model to allow explicit estimation of the between therapy group variance.

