#### Primary outcome

The primary outcome is social functioning, measured by the Social Functioning Questionnaire (SFQ) [23]. The SFQ is an 8-item self-report scale, with items covering the domains of home, work, leisure, and relationships. Respondents rate the extent to which they have experienced problems in each area over the last two weeks on a scale from 0 to 3. SFQ scores correlate well with measures of psychiatric distress and are stable over time. A reduction (i.e., an improvement) of 2 points or more on the SFQ at follow up 72 weeks post-randomisation is our specified clinically significant change.

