### Analyses

Demographic and other baseline data will be summarised by descriptive statistics (number [N], mean, standard deviation [SD], median, minimum and maximum) or frequency tables, stratified by treatment. Measures of adherence to protocol implementation will be summarised by descriptive statistics (number [N], mean, standard deviation [SD], median, minimum and maximum) or frequency tables, stratified by treatment arm. Efficacy will be assessed on the full analysis set, defined as all randomised participants for whom a post-baseline assessment of the primary endpoint is available, that is, in accordance with the "intention to treat" (ITT) principle. The primary efficacy parameter will be the difference in mean SFQ score between treatment arms, estimated using a hierarchical regression model with adjustment for relevant covariates, including centre, sex and personality disorder classification. Differences in mean totals of secondary outcomes at 72 weeks from randomisation will be compared between the two treatment arms, after adjusting for design (centre and sex) covariates. Analyses will be performed using Stata version 11 or above.

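### The secondary models adjust for centre and sex but not for baseline values the trial collects, and the primary model does not name baseline SFQ: a free gain in precision is left unclaimed

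*Protocol article*

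**What the plan says.** **Primary model.** The Analyses section takes the difference in mean SFQ score between arms as the efficacy parameter, "estimated using a hierarchical regression model with adjustment for relevant covariates, including centre, sex and personality disorder classification". Baseline SFQ is not among the three named covariates. The word *including* leaves the list open.

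**Secondary models.** The same section compares mean totals of the secondary outcomes at 72 weeks "after adjusting for design (centre and sex) covariates". The parenthesis spells out which covariates are meant, so this reads as a fixed set.

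**What is measured before treatment.**
- SFQ: a baseline score is implied, because the Primary outcome section defines clinically significant change as a reduction of 2 points or more.
- EQ-5D and client-rated problems: pre-treatment assessment is stated in their own sections.
- CSRI service use: the 6 months before baseline are covered.
- GAF: the outcome is described as a change in the referrer's score, which implies an earlier rating.
- HADS: the text gives no assessment times, and the procedural flow diagram is not shown.
- Record check of scheduled and unscheduled service use: data run from baseline to 72 weeks, with no earlier period stated.

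**Hypothesis and background.** Study Hypotheses says that "those in PEPS therapy will show a greater improvement in social functioning". Primary outcome says that "SFQ scores correlate well with measures of psychiatric distress and are stable over time".

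**The concern.** For a questionnaire score, the same person's earlier score on the same scale is usually one of the most informative covariates available. The article goes beyond the stratification factors to name personality disorder classification, yet does not name baseline SFQ. For the secondary outcomes it goes further and states an adjustment set without baseline values.

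Precision is what is at stake. If baseline and 72-week scores are correlated, a model without the baseline leaves explainable variance in the residual, and confidence intervals are wider than the data require. On the primary outcome there is a second, smaller matter: whether a potentially influential covariate enters the model is left open when it could be fixed in advance in a few words.

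**Working it through.** **Inputs from the Sample size section.** The target is given as "To detect a mean difference in SFQ score of 2 point (SD = 4.53) at 72 weeks". The error rates are given as "two-sided significance level of 1% and power of 80" percent. Allocation is equal, with 120 evaluable per arm, inflated to 170 per arm for 30% drop-out. On the choice of SD: "We have based our sample size estimate on the most conservative (i.e., largest) SD". It is a raw SD, with no reduction for baseline adjustment.

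**Step 1: reproduce the plan's own figure.**

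n per arm = 2 × [SD × (z₀.₉₉₅ + z₀.₈₀) / difference]² = 2 × [4.53 × (2.576 + 0.842) / 2]² = 119.8, rounded up to 120. This matches the stated 120.

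Drop-out: 120 / 0.70 = 171.4, so 172 per arm against the stated 170. In reverse, 170 × 0.70 = 119, at which power is 79.7%. The difference is negligible.

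Power at 120 per arm, unadjusted: SE = 4.53 × √(2/120) = 0.585, and power = Φ(2/0.585 − 2.576) = 80.1%. The planned power therefore holds with no baseline covariate in the model.

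**Step 2: add baseline SFQ.** With correlation r between baseline and 72-week SFQ, the residual SD is 4.53 × √(1 − r²). The article gives no value of r. Its remark on stability carries no interval and no coefficient, so the range below is an assumption.

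| Assumed r | Residual SD | SE of difference | Power at 120 per arm | Fall in residual variance | n per arm for 80% power |
|---|---|---|---|---|---|
| 0 (no adjustment) | 4.53 | 0.585 | 80.1% | 0% | 120 |
| 0.3 | 4.32 | 0.558 | 84.4% | 9% | 110 |
| 0.5 | 3.92 | 0.506 | 91.5% | 25% | 90 |
| 0.7 | 3.24 | 0.418 | 98.7% | 49% | 62 |

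The last column only expresses the gain in participants. It does not suggest a smaller trial.

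**Step 3: is chance baseline imbalance a separate harm?** Assume the same SD at baseline. The SE of the baseline difference is then also 0.585. At r = 0.5, an imbalance of one SE shifts the unadjusted estimate by 0.5 × 0.585 = 0.29 points. The unadjusted variance is 0.585² = 0.342 and the adjusted variance is 0.506² = 0.256. The difference is 0.086, and its square root is 0.29. The imbalance is thus the same quantity as the precision loss in the table, already contained in the unadjusted SE, and must not be counted twice.

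**Secondary outcomes.** The same formula applies to each outcome with a measured baseline, but the article gives neither SDs nor correlations for them, so no size is claimed.

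**The case against.** The strongest reply is that nothing here is an error. Most of it stands.

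- **The primary list is open.** A reader might infer that precision on the primary outcome is being discarded. The text does not show this: *including* allows baseline SFQ, and the statistical analysis plan, not available here, may add it. What remains is that the article does not name it.
- **The estimand is sound.** A reader might infer that comparing 72-week means misses a hypothesis about improvement. Under randomisation the expected baseline means are equal, so the difference in 72-week means and the difference in mean change have the same expectation.
- **Planned power is not short.** The sample size rests on the largest unadjusted SD, so any gain comes on top of the plan.
- **The exploratory work is not a precedent for the treatment comparison.** The Background phrase "after controlling for baseline level of social functioning" describes an analysis of which problem-solving changes predicted improvement. It does not show the investigators departing from their own treatment-effect model.
- **QALYs.** A reader might infer that the QALY difference will ignore baseline utility. The centre-and-sex sentence concerns secondary outcome totals, and the economic paragraphs state no covariate set either way.
- **Uneven secondary outcomes.** GAF as a change score already uses its baseline, HADS timing is not stated, and the record check has no prior value.

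On the other side, drop-out of 30% is allowed for, and the full analysis set requires a post-baseline SFQ. Conditioning on baseline can make a missing-at-random assumption more plausible. That is a further reason to adjust, but the article gives no sign that drop-out depends on baseline differently by arm, so no bias is claimed.

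The reply does not remove the adjustment set stated for the secondary outcomes, which omits values the trial collects.

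**Conclusion.** The point holds as a matter of efficiency and clarity, and it is an improvement at almost no cost rather than a correction of an error. It is firmest for the secondary outcomes, where the adjustment set is stated. For the primary outcome it is limited to a covariate left unnamed in an open list.

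For SFQ, the gain over the reproduced 80.1% is about 4, 11 or 19 percentage points of power at correlations of 0.3, 0.5 or 0.7. This rests on the planned difference and SD, 120 evaluable per arm, a linear baseline effect and the normal approximation. The correlation is assumed throughout. A low value would make the gain modest.

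**What to change.** 1. **Primary model:** name baseline SFQ, as a continuous covariate, beside centre, sex and personality disorder classification.
2. **Secondary models:** add to centre and sex the outcome's own baseline value wherever one is measured. This covers EQ-5D, client-rated problems and CSRI service use, and GAF and HADS if they are taken at baseline. Leave the record-check outcome at centre and sex, since no prior value is stated for it.
3. **Economic analysis (recommendation only):** adjust the QALY difference for baseline EQ-5D, and say so, as no covariate set is given at present.

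The cost is a sentence or two in the protocol and the analysis plan, made before any unblinded look at the data. No extra participants are needed, and no new data for outcomes whose baseline is already collected. The sample size calculation can stay as it is.

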### Randomisation and blinding

Randomisation is based on a computer generated pseudo-random code using random permuted blocks of randomly varying size, created by the Nottingham Clinical Trials Unit (CTU) in accordance with their standard operating procedure and held on a secure server. The randomisation is stratified by recruiting centre and sex of participant. Access to the sequence is confined to the Trial Data Manager. Researchers access the treatment allocation for each participant by means of a remote, internet-based randomisation system developed and maintained by the Nottingham CTU. The sequence of treatment allocations will be concealed until interventions have all been assigned and recruitment, data collection, and all other trial-related assessments are completed. The trial is single-blind, with participants and local investigators administering the interventions being aware of the treatment allocation. Outcome measures are administered in a blinded fashion by researchers to minimise the effects of lack of blinding.

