##### Receipt and cost of services

(Client Service Receipt Inventory; CSRI [31]). One measure used to capture service use is the CSRI, which records health and social care, criminal justice, informal care services, employment and benefits as reported by the participant. This information will be used in the cost-effectiveness analysis. Service use will be assessed for the period 6 months prior to baseline, and at three points after treatment (immediately after, at 4 months and at 72 weeks). The long-term follow up is necessary to pick up potential improvement overall, rather than capture a temporary increase at the end of treatment.

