##### Quality of life

(EuroQOL; EQ-5D) [32]. The EQ-5D is a health-related quality of life measure and will be used to generate quality-adjusted life years for use in the economic evaluation. The EQ-5D will be administered before and after treatment, and again at 72 week follow-up.

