The costs of the interventions will be estimated by combining data on number of sessions provided with unit costs derived from local data on service expenditure and activity. These costs will include therapist time, oncosts, overheads and capital. Costs of other services will be calculated by combining service use data collected with the CSRI with appropriate unit costs. Costs will be compared between the two groups, with bootstrap methods used to generate confidence interval round the difference due to the expected skewed cost distribution. Cost-effectiveness will be assessed by combining the cost adapt with outcomes, namely SFQ scores and Quality-Adjusted Life Years (QALYs). If the costs for the PEPS arm are less than for TAU and the outcome better, then it will be the 'dominant' intervention. However, if costs are greater and outcomes better, then an incremental cost-effectiveness ratio will indicate the extra costs incurred to achieve an extra unit-improvement in outcome (i.e., a one-point improvement on the SFQ or one extra QALY). There will be uncertainty around the point estimates of cost and outcome differences and this uncertainty will be explored by generating a large number of cost-outcome combinations using bootstrapped resample and plotting these on a cost-effectiveness plane. Cost-effectiveness will be interpreted using cost-effectiveness acceptability curves. These will show the probability that PEPS is more cost-effective intervention than TAU for a range of values placed on a unit-improvement in outcome. The range of values for a one-point improvement on the SFQ is unclear, but will be chosen such that we will be able to observe the points at which there is at least at 50% and 80% probability of PEPS being cost-effective. The range of values for a gain of one QALY is more straightforward as it appears that the value that informs NICE recommendations is between £20-30K. Therefore we will use a range of £0-£100K to produce the curve so as to include this threshold.

Thematic analysis methods will be used to specify the nature of treatment-as-usual in terms of what problem was treated by which service/professional and how. Thematic analysis methods will be used to identify themes in participants' opinions of PEPS therapy and TAU.

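### The economic comparison names no baseline adjustment for costs or QALYs, although the baseline EQ-5D and pre-baseline service use needed for it are collected

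*Protocol article*

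**What the plan says.** Cost-effectiveness is the second study aim. The economic part of the Analyses section describes the cost contrast as follows: "Costs will be compared between the two groups, with bootstrap methods used to generate confidence interval round the difference due to the expected skewed cost". Joint uncertainty is handled by "generating a large number of cost-outcome combinations using bootstrapped resample and plotting these on a cost-effectiveness plane", and acceptability curves follow. The two effectiveness measures are SFQ and QALYs. The QALY curve runs from £0 to £100K so as to include the threshold, on the view that "the value that informs NICE recommendations is between £20-30K". No covariate appears anywhere in this account.

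The paragraph before it does name covariates for the clinical outcomes: centre, sex and personality disorder classification for the primary outcome (an open list), and for the secondary outcomes a comparison at 72 weeks "after adjusting for design (centre and sex) covariates". Neither list names a baseline value.

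The inputs for a baseline adjustment exist. Under Quality of life: "The EQ-5D will be administered before and after treatment, and again at 72 week follow-up". Under Receipt and cost of services: "Service use will be assessed for the period 6 months prior to baseline, and at three points after treatment". Under Randomisation and blinding: "The randomisation is stratified by recruiting centre and sex of participant", so neither prior service use nor baseline utility is balanced by design.

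**The concern.** The article goes into some detail on the economic method, and it names covariates for the clinical comparisons immediately beforehand. A reader who carries out the economic paragraph as written will bootstrap unadjusted differences.

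For costs, that gives up precision: prior service use usually predicts later service use, and it is already recorded.

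For QALYs there is more to it. If QALYs are computed as the area under the utility curve, baseline utility is the first point of that curve. A chance difference in baseline EQ-5D then enters the QALY difference twice: directly through that first point, and indirectly because later utilities correlate with it. Resampling the realised data does not remove this. The cloud on the plane is centred on the observed difference, imbalance included. At stake are the precision and the realised position of the ICER and acceptability curves.

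**Working it through.** **Inputs from the documents.** The design requires 120 evaluable participants per arm (Sample size). That figure reproduces: 2 × (2.576 + 0.842)² × 4.53² / 2² = 119.9, rounded up to 120. I use it only to set the sample size for what follows; 170 per arm are to be recruited. EQ-5D is taken before treatment, after treatment and at 72 weeks.

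**Assumptions, not in the documents.** QALYs are computed as the area under the curve by the trapezoid rule. The EQ-5D SD is 0.30 (range 0.25-0.35) and equal at all occasions. The correlation ρ is 0.5 (range 0.4-0.7) and equal between all pairs of occasions. The post-treatment assessment is at week T = 28 (range 20-36).

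**Step 1: weights.** In years, the three utilities carry weights w0 = (T/2)/52, w1 = 36/52 and w2 = ((72 − T)/2)/52. At T = 28 these are 0.269, 0.692 and 0.423.

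**Step 2: slope of the QALY on baseline utility.** b = w0 + ρ(w1 + w2) = 0.269 + 0.5 × (0.692 + 0.423) = 0.827.

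**Step 3: chance imbalance.** The standard error of the baseline difference is SD × √(2/n) = 0.30 × √(2/120) = 0.0387.

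**Step 4: carry-over with no treatment effect.** 0.827 × 0.0387 = 0.032 QALY for a one-standard-error imbalance.

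**Step 5: variance removed by adjustment.** The QALY variance in units of SD² is w0² + w1² + w2² + 2ρ(w0w1 + w0w2 + w1w2) = 1.324. The share explained by baseline utility is b²/1.324 = 0.684/1.324 = 0.52. The standard error of the QALY difference falls from √1.324 × 0.0387 = 0.0446 to 0.0446 × √(1 − 0.516) = 0.031.

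**Step 6: range, varying SD, ρ and T together.**

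| | Lowest | Central | Highest |
|---|---|---|---|
| SD, ρ, T for the shift | 0.25, 0.4, 20 | 0.30, 0.5, 28 | 0.35, 0.7, 36 |
| QALY shift per one-standard-error imbalance | 0.022 | 0.032 | 0.048 |
| Shift valued at £20K per QALY | £440 | £640 | £960 |
| Shift valued at £30K per QALY | £660 | £960 | £1,440 |
| QALY variance removed by adjustment | 37% | 52% | 74% |

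The variance share does not depend on SD. With 170 per arm, the shifts are multiplied by √(120/170) = 0.84, giving about 0.018-0.041.

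**Step 7: costs.** Adjusting for a baseline cost that correlates r with follow-up cost multiplies the standard error by √(1 − r²). For assumed r of 0.3, 0.5 and 0.7 this is 0.954, 0.866 and 0.714, a reduction of about 5% to 29%. The documents give neither r nor a cost SD.

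**The case against.** The strongest reply is that silence is not a decision. The bootstrap is offered as an interval method for skewed costs, and it applies just as well to a regression-adjusted difference. Nothing in the paragraph rules covariates out. A journal article may leave the covariate list, like the QALY construction, to an analysis or health-economics plan that is not shown. Quality of life and receipt and cost of services are also listed as secondary outcomes, so the centre-and-sex adjustment may have been meant to reach the economic data.

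Much of this stands. A reader might infer that the investigators chose against adjustment; the text does not say so. It is also unclear whether the centre-and-sex adjustment extends to costs and QALYs. But that adjustment names no baseline value, and it concerns outcomes at 72 weeks rather than QALYs or the ICER, so it does not supply what is missing here. The economic method is otherwise described fully enough to be followed as it stands, and doing so leaves a free gain unused.

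A second reply is that chance imbalance is ordinary sampling error, already counted in the bootstrap interval. This is correct. A reader might infer that the planned analysis is biased or its intervals invalid. Under randomisation neither is so. What remains is lost precision, and error conditional on whatever imbalance the realised sample happens to show.

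**Conclusion.** The point holds as an improvement to a described method. It is not an error or a contradiction, and no stated figure is disputed. As written, the economic comparison names no baseline adjustment although the data for it are collected. Under the stated assumptions a one-standard-error chance imbalance in EQ-5D moves incremental QALYs by about 0.022-0.048, which is not negligible at £20-30K per QALY, and adjustment would remove about 37%-74% of the QALY variance. These sizes rest on an assumed SD, correlation, visit timing and area-under-the-curve QALYs, and they apply only if the analysis is in fact unadjusted.

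A reader might want to turn the shift into a probability of cost-effectiveness, or the cost gain into statistical power. The documents do not support either step. The first needs the variance of the cost difference, which is not given. For the second, the stated power and significance level belong to the SFQ comparison only.

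**What to change.** In the economic part of Analyses, state that:

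- incremental QALYs are estimated by regression, adjusting for baseline EQ-5D utility, centre and sex;
- incremental costs are adjusted for CSRI-based cost in the 6 months before baseline, centre and sex;
- the SFQ difference used in the SFQ-based ratio is adjusted for baseline SFQ, centre and sex;
- these models are refitted within every bootstrap resample, and the ICER, plane and acceptability curves are built from the adjusted differences;
- unadjusted results are reported as a sensitivity analysis.

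This should be fixed before baseline data by arm are seen, because a choice made after seeing an imbalance would be open to criticism. If an unpublished plan already specifies it, a sentence saying so is enough. The cost is some wording and a little code, with no new data. The one small downside is that participants with a missing baseline value will need simple imputation.
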